### Analytical techniques

To compare the % uptake of preschool immunisation across time-periods we will visualise the total % uptake within 4 weeks of eligibility for each time-period by vaccine in a bar plot.

To statistically test whether these uptake rates are different, we will perform a binary logistical regression analysis for aggregate data, using time period as the explanatory variable, and vaccination status (vaccinated or unvaccinated) as the dependent variable. Separate analyses will be carried out for each vaccine. Odds ratios with 95% confidence intervals will be calculates using 2019 as the baseline comparator.

The following tables will be utilised:

Table 5 Odds of being vaccinated between time-periods for each vaccine visit

| Vaccine | Time-period comparison | Odds ratio | 95% CI |
| --- | --- | --- | --- |
| First dose 6in1 | 2019 vs pre-lockdown (secondary outcome) |  |  |
|  | **2019 vs lockdown (primary outcome)** |  |  |
|  | Pre-lockdown vs lockdown (secondary outcome) |  |  |
|  | 2019 vs post-lockdown (secondary outcome) |  |  |
|  | Lockdown vs post-lockdown (secondary outcome) |  |  |
| Second dose 6in1 | 2019 vs pre-lockdown (secondary outcome) |  |  |
|  | **2019 vs lockdown (primary outcome)** |  |  |
|  | Pre-lockdown vs lockdown (secondary outcome) |  |  |
|  | 2019 vs post-lockdown (secondary outcome) |  |  |
|  | Lockdown vs post-lockdown (secondary outcome) |  |  |
| … |  |  |  |
| Second dose MMR | 2019 vs pre-lockdown (secondary outcome) |  |  |
|  | **2019 vs lockdown (primary outcome)** |  |  |
|  | Pre-lockdown vs lockdown (secondary outcome) |  |  |
|  | 2019 vs post-lockdown (secondary outcome) |  |  |
|  | Lockdown vs post-lockdown (secondary outcome) |  |  |

### Potential confounders

None available since aggregated data

### Potential effect modifiers

None at this stage

### Sub-group analysis

None

### Corrections for multiple testing

None

### Sensitivity analysis

None

### Other analysis

None

## Objective bi) Explore the difference in impact between geographical areas

### Outcome

Absolute/relative difference in % uptake within 4 weeks of eligibility during lockdown vs 2019 for each Health and Social Care Partnership (HSCP).

### Exposures of interest

Geographical area, specifically HSCP (excluding partnership areas within NHS Grampian for the MMR second dose only).

### Analytical techniques

To visualise the spatial distribution of the difference in lockdown and 2019, the % differences will be plotted in a choropleth map of Scotland segmented into HSCPs. This map will have each HSCP area coloured according to the % difference. This will be repeated for each vaccine type.

To statistically test whether these uptake rates are different between time periods for each HSCP, we will perform a binary logistical regression analysis for aggregate data, using vaccination status (vaccinated or unvaccinated) as the dependent variable and time period as the explanatory variable, specifying an interaction with HSCP. Separate analyses will be carried out for each vaccine. Odds ratios with 95% confidence intervals will be calculated using 2019 as the baseline comparator and results will be visualised using forest plots. The following table will be used (one for each vaccine):

Table 6 Odds of being vaccinated between time-periods by HSCP

| Time-period | Variable | Difference % | Odds ratio | 95% CI |
| --- | --- | --- | --- | --- |
| 2019 vs lockdown | Aberdeen City |  |  |  |
|  | Aberdeenshire |  |  |  |
|  | Angus |  |  |  |
|  | … |  |  |  |

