## Objectives

We seek to:

1. Describe the impact of the COVID-19 pandemic on the uptake of selected immunisations provided at each of the five immunisation contacts offered to pre-school children (table 1)
2. Explore whether impact varied by: i) Health and social care partnership area of residence (HSCP- geographical areas closely related to local authority areas); and ii) socio-economic deprivation index
3. Use these data to inform future strategies to promote maximal childhood vaccine uptake and reduce barriers, both in the context of a pandemic and more generally.

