### Analytical techniques

To explore the difference in the % uptake during lockdown (23Mar-Jul 2020) versus 2019 across the deprivation quintiles, we will plot the % difference for each vaccine by the SIMD quintile in a bar plot.

To statistically test whether these uptake rates are different between time periods for each SMID quintile, we will perform a binary logistical regression analysis for aggregate data, using time period as the explanatory variable, and vaccination status (vaccinated or unvaccinated) as the dependent variable, specifying an interaction with SIMD quintile. Separate analyses will be carried out for each vaccine. Odds ratios with 95% confidence intervals will be calculated using 2019 as the baseline comparator. The following tables will be utilised (one for each vaccine):

Table 7 Odds of being vaccinated between time-periods by SMID

| Time-period | Variable | Difference % | Odds ratio | 95% CI |
| --- | --- | --- | --- | --- |
| 2019 vs lockdown | SMID 1 |  |  |  |
|  | SMID 2 |  |  |  |
|  | SMID 3 |  |  |  |
|  | SMID 4 |  |  |  |
|  | SMID 5 |  |  |  |

A similar technique will be carried out to determine the odds of being vaccinated by SMID quintile at each time point (2019 and lockdown), using SMID 1 (most deprived) as the baseline comparator, to assess for change in the inequality between SMID quintiles between the two time periods.

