# Reporting results

## Reporting guidelines and conventions

Results will be reported according to STROBE (11) and RECORD (12) (via the COVID-19 extension) guidelines. P-values will be quoted to two decimal places, unless they are less than 0.001 (whereby the p-value will be given as <0.001) or between <0.005 and >0.001, in which case they will be stated to three decimal places. We will report 95% confidence intervals and if the confidence intervals cross 1, the results will not be considered statistically significant.

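### Objective 2 asks whether impact varied by area and deprivation, but the planned tests and tables report only the change within each stratum

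*SAP*

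**What the plan says.** The SAP's Objectives section sets the question as "Explore whether impact varied by: i) Health and social care partnership area of residence", and adds socio-economic deprivation as the second factor.

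Under Objective bi, Analytical techniques, the hypothesis and its test are stated as "To statistically test whether these uptake rates are different between time periods for each HSCP, we will perform a binary logistical regression analysis". The logistic model for it takes "time period as the explanatory variable, specifying an interaction with HSCP". The output is "Table 6 Odds of being vaccinated between time-periods by HSCP": one 2019-versus-lockdown row per area, with the percentage difference, the odds ratio and its 95% CI. Forest plots and maps accompany it.

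Under Objective bii, the wording is parallel: "To statistically test whether these uptake rates are different between time periods for each SMID quintile", again with an interaction in the model, and Table 7 has one row per quintile. A further analysis compares quintiles with SIMD 1 in 2019 and in lockdown, "to assess for change in the inequality between SMID quintiles between the two time periods".

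The only decision rule is in Reporting guidelines and conventions: "if the confidence intervals cross 1, the results will not be considered statistically significant". Neither table has a row for an interaction test, a ratio of odds ratios or a trend, and the text names none of these.

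**The concern.** Whether uptake changed in a given stratum and whether the change differed between strata are two different hypotheses. Objective 2 poses the second; the stated tests address the first. The model is the right one, but the part of its output that answers the objective (the interaction terms) has no place in the plan's reported results.

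With a full period-by-stratum model, the stratum-specific odds ratios are the same as those from fitting each stratum separately, so including the interaction does not by itself bring any comparison between strata into the results. What remains is a list of intervals, each judged against 1. A precise interval from a large area excludes 1 more readily than a wide one from a small area, even when the underlying effect is the same. If the pattern of significant and non-significant strata is taken as the answer to Objective 2, areas may be described as differently affected for reasons of size alone. A statement that inequality widened or narrowed would likewise have no interval behind it. Objective 3 and the Dissemination section carry these results to policy and delivery leads, so such statements have consequences.

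**Working it through.** The SAP gives no power, effect size or stratum counts (it takes the entire eligible population), so there is no figure of its own to reproduce. The check has two parts.

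**1. Question against test.**

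| Item | Objective 2 | Planned output |
|---|---|---|
| HSCP | Does the period effect differ across areas? | Period effect in each area, CI against 1 |
| SIMD | Does the period effect differ across quintiles? | Period effect in each quintile, CI against 1 |
| Inequality | Change in the quintile gap | Quintile odds ratios in 2019 and in lockdown; no estimate or test of the change |

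The quantity needed is the ratio of odds ratios between strata, or a joint test that all such ratios equal 1. Neither is specified.

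**2. How the within-stratum tests behave when impact is identical everywhere.**

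From the SAP: lockdown is 19 weekly cohorts (weeks beginning 23 March to 27 July 2020), or 133 days, against the whole of 2019; two-sided 5% level. Assumptions: stratum size n per year, 2019 uptake p0 = 0.90, and a common odds ratio (OR). Lockdown n1 = n × 133/365.

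- Lockdown uptake: p1 = o/(1 + o), with o = OR × p0/(1 − p0).
- SE(log OR) = √[1/(n·p0·(1 − p0)) + 1/(n1·p1·(1 − p1))].
- Power = Φ(z − 1.96) + Φ(−z − 1.96), with z = |log OR|/SE.

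*HSCPs, OR = 0.70.* o = 9 × 0.70 = 6.3 and p1 = 0.863. For n = 250, n1 = 91.1; SE = √(0.0444 + 0.0929) = 0.371; z = 0.357/0.371 = 0.963; power 16%.

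| Eligible per year | SE(log OR) | Power |
|---|---|---|
| 250 | 0.371 | 16% |
| 500 | 0.262 | 28% |
| 1,000 | 0.185 | 49% |
| 2,000 | 0.131 | 78% |
| 4,000 | 0.093 | 97% |

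A simulation (4,000 runs per scenario; 20 or 30 areas with 2019 cohorts spaced geometrically from 200 to 6,000; uptake 85% or 95%; common OR 0.80, 1.25 or 1.50) gives the same picture. A mix of significant and non-significant areas appeared in 95% to 100% of runs. A joint homogeneity test declared variation in 2.2% to 4.7%, at or below its nominal 5%. With 30 areas, 85% uptake and OR 0.80, about 12 areas were significant on average: the smallest in 11% of runs, the largest in 91%.

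*Quintiles, n = 10,000 each in 2019, n1 = 3,644.* With P the power in one quintile, the chance of a mixed pattern across five is 1 − P⁵ − (1 − P)⁵. At OR 0.90: SE = 0.063, z = 0.105/0.063 = 1.68, P = 0.391, and 1 − 0.009 − 0.084 = 0.907.

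| Common OR | Power per quintile | Chance of mixed pattern |
|---|---|---|
| 0.90 | 39% | 91% |
| 0.85 | 75% | 76% |
| 0.80 | 96% | 20% |
| 0.75 | 99.8% | 1% |
| 0.70 | >99.9% | about 0.01% |

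These quintiles are equal in size, so the mixed pattern here is sampling noise at middling power, not an effect of stratum size.

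**The case against.** The strongest reply is that the model already contains the interaction. Its coefficients are log ratios of odds ratios with standard errors, so the answer to Objective 2 exists once the model is fitted. A reader might infer that the analysis is of the wrong kind and cannot address the objective; the SAP does not support that. The fault is that the relevant output is neither named nor tabulated, while a different hypothesis is named in its place.

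A reader might also infer that the change in inequality will be judged by eye from two lists. The SAP does not say so. It states the intention, refers to a similar technique, and is silent on the estimate or test.

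Nor does the SAP say that non-significant areas will be called unaffected. The objective is worded as exploratory, and the maps, forest plots and percentage differences show magnitude and precision. Misreading is therefore a risk, not a certainty. Against that, the plan itself chooses to test formally and sets a significance rule, and that rule is attached only to within-stratum odds ratios.

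The quintile risk depends heavily on the assumed odds ratio and almost vanishes at 0.70. That stands, as does the limit on the size mechanism, which applies mainly to HSCPs. A count of unadjusted area-level tests across vaccines would need the number of HSCPs, which the SAP does not give. The absence of a multiplicity correction is a declared choice and is not part of this point.

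**Conclusion.** The concern holds as a mismatch between objective and reported inference. The interaction is fitted but used only for within-stratum comparisons, and the change in inequality has no specified estimate or test. This is more than missing detail, because the test that is stated answers a different question.

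For HSCPs the consequence is substantial over the size range assumed: power runs from about 16% to 97% under identical impact. For quintiles it runs from serious (91% chance of a mixed pattern at a common OR of 0.90) to negligible (at 0.70). All these figures rest on assumed uptake, stratum sizes and odds ratios. The mismatch itself rests on the SAP's text alone.

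**What to change.** For each vaccine, from the model already specified:

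- Report the joint likelihood-ratio test of period × HSCP and of period × SIMD (4 df), restricted to 2019 and lockdown. Use an F test instead if the model is dispersion-scaled.
- For SIMD, report ratios of odds ratios with 95% CIs (quintiles 2 to 5 against quintile 1, lockdown relative to 2019) as the estimate of change in inequality. A 1-df trend across ordered quintiles is a useful option.
- Keep Tables 6 and 7 as the stratum-specific description, with an added line for the joint test.
- State that significance in one stratum and not in another will not be read as a difference in impact.

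The cost is a few sentences in the SAP and a few lines of R on the same aggregate counts. Whether statements about individual areas should depend on the joint test is a matter of preference and need not be settled for this correction.

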### Potential confounders

None

### Potential effect modifiers

None

### Sub-group analysis

None

### Corrections for multiple testing

None

### Sensitivity analysis

None

### Other analysis

None

## Objective bii) Explore the difference in impact between socio-economic deprivation

### Outcome

Absolute/relative difference in % uptake within 4 weeks of eligibility during lockdown vs total 2019 by SMID quintile.

### Exposures of interest

Scottish Index of Multiple Deprivation (SIMD) quintiles

### Analytical techniques

To explore the difference in the % uptake during lockdown (23Mar-Jul 2020) versus 2019 across the deprivation quintiles, we will plot the % difference for each vaccine by the SIMD quintile in a bar plot.

To statistically test whether these uptake rates are different between time periods for each SMID quintile, we will perform a binary logistical regression analysis for aggregate data, using time period as the explanatory variable, and vaccination status (vaccinated or unvaccinated) as the dependent variable, specifying an interaction with SIMD quintile. Separate analyses will be carried out for each vaccine. Odds ratios with 95% confidence intervals will be calculated using 2019 as the baseline comparator. The following tables will be utilised (one for each vaccine):

Table 7 Odds of being vaccinated between time-periods by SMID

| Time-period | Variable | Difference % | Odds ratio | 95% CI |
| --- | --- | --- | --- | --- |
| 2019 vs lockdown | SMID 1 |  |  |  |
|  | SMID 2 |  |  |  |
|  | SMID 3 |  |  |  |
|  | SMID 4 |  |  |  |
|  | SMID 5 |  |  |  |

A similar technique will be carried out to determine the odds of being vaccinated by SMID quintile at each time point (2019 and lockdown), using SMID 1 (most deprived) as the baseline comparator, to assess for change in the inequality between SMID quintiles between the two time periods.

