## Sample size calculation

Taking in entire eligible population

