# Data and data validation

## Data variables available

Table 2 Available variables (Scottish dataset)

| **Variable** | **Description** | **Values** |
| --- | --- | --- |
| Vaccine type | Type of preschool immunisation vaccine | First dose 6in1 (8 weeks)  Second dose 6in1 (12 weeks)  Third dose 6in1 (16 weeks)  First dose MMR (12 months)  Second dose MMR (3 years and 4 months) |
| Area name | Splits into Scotland as a whole, NHS Health Boards and HSCP | Scotland  NHS Health Boards  HSCP |
| Time-period | Time-period when preschool child was eligible for immunisation | 2019 (baseline),  January to September 2020 (Monthly)  Week beginning 02 March to 28 September 2020 (Weekly) |
| Total eligible | The total number of eligible preschool children | N |
| Total uptake within 4 weeks of eligibility (N)* | The number of preschool children who received vaccination within 4 weeks of becoming eligible | N |
| Total uptake within 4 weeks of eligibility (%) | The number of preschool children who received vaccination within 4 weeks of becoming eligible out of the total number of eligible preschool children | % [0,100] |
| SIMD Quintile (for Scotland level data only) | Scottish Index of Multiple Deprivation (SMID) index | 1 (most deprived), 2, 3, 4, 5 (least deprived) |

*Note: Data are available for total uptake at later ages (for example 6 months of age). However, we have chosen to examine uptake within 4 weeks of eligibility as this represents timely uptake of vaccinations as per the recommended schedule.

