### Exposures of interest

Time, specifically in time-periods: 2019 (baseline), 01 Jan- 22 Mar 2020 (pre-lockdown), 23 Mar-final week Jul 2020 (lockdown) and Aug-end of Sept 2020 (post lockdown). The start date to 23 Mar has been chosen to correspond with the beginning of the UK wide lockdown as announced by the UK government. The end of the lockdown period is less well-defined and varied both in approach and timescale between Scotland, England, Wales and Northern Ireland. Broadly speaking, by the end of July, there was a substantial reduction in ‘lockdown’ restrictions with the opening of many non-essential businesses and limited indoor meeting between households permitted, therefore a pragmatic approach has been taken to define the lockdown period as 23 Mar 2020 until end Jul 2020. The data included in each time period are shown in Table 4.

Table 4 Definition of time periods

| Time period | Data included |
| --- | --- |
| Baseline 2019 | Aggregate data for whole of 2019 |
| Pre-Lockdown 2020 | Monthly data for Jan 2020 and Feb 2020. Weekly data from W/B 2Mar2020 up to and including W/B 16Mar2020 |
| Lockdown 2020 | Weekly data from W/B 23Mar2020 up to and including W/B 27Jul2020 |
| Post lockdown 2020 | Weekly data from W/B 3Aug2020 up to and including W/B 28Sept2020 |

The primary outcome of interest is comparison between baseline 2019 and lockdown 2020 for each vaccine. Of secondary interest are comparisons between baseline 2019 and pre-lockdown 2020, baseline 2019 and post lockdown 2020, pre-lockdown 2020 and lockdown 2020, lockdown 2020 and post lockdown 2020.

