### Corrections for multiple testing

None

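### The deprivation analysis sets out to assess change in inequality but plans no estimate or confidence interval for that change, and it does not use the order of the SIMD quintiles

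*SAP*

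**What the plan says.** Table 2 of the SAP (Data variables available) lists SIMD as an ordered scale: "1 (most deprived), 2, 3, 4, 5 (least deprived".

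Under objective bii, Analytical techniques, two analyses are planned for each vaccine.

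- A logistic regression on aggregate counts with time period as explanatory variable, "specifying an interaction with SIMD quintile". Table 7 takes its output as one lockdown-versus-2019 difference, odds ratio and CI per quintile. SIMD therefore enters as a five-level factor. A bar plot shows the percentage difference by quintile.
- A second set of models of the same kind, "to determine the odds of being vaccinated by SMID quintile at each time point (2019 and lockdown". The reference group for these odds ratios, and the reason for producing them, are then stated as follows: "using SMID 1 (most deprived) as the baseline comparator, to assess for change in the inequality between SMID quintiles between the two time periods".

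The Reporting section gives the only decision rule: "We will report 95% confidence intervals and if the confidence intervals cross 1, the results will not be considered statistically significant". Within objective bii, the entries under "Corrections for multiple testing", sensitivity analysis and other analysis all read None. The sample size section says only "Taking in entire eligible population", so the plan has no power figure to reproduce.

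**The concern.** The second analysis has a stated purpose, change in inequality, but its output is two sets of four odds ratios, one set per period. Across five vaccines that is 8 × 5 = 40 odds ratios, and none of them measures a change. The rule on intervals that cross 1, applied to these odds ratios, tests whether quintiles differ within a period. It does not test whether the difference altered between periods. The odds ratios in Table 7 are changes over time within a quintile, so they do not compare quintiles either.

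The quintiles are ordered, and a widening or narrowing gradient is a natural form for a change in inequality to take. No trend term, slope or relative index of inequality is named. The reader is left to weigh eight numbers that share one reference quintile per period, may point in different directions, and come with no rule for reading them together. The SAP intends its results to inform future uptake strategies, so an unclear answer on inequality would matter.

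**Working it through.** **Does any planned output estimate the change?** Let OR(k, period) be the odds ratio of quintile k against SIMD 1 in a period. The change in inequality for quintile k is

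ROR(k) = OR(k, lockdown) / OR(k, 2019).

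This equals the Table 7 odds ratio for quintile k divided by the Table 7 odds ratio for SIMD 1, and its logarithm is the period-by-SIMD interaction coefficient. The planned model therefore contains the quantity, but no table or sentence asks for it, for its CI or for a joint test.

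**Relative power.** Inputs: five ordered quintiles (Table 2); two-sided alpha 0.05 (from the 95% CIs). Assumptions: equal information w per quintile on the change in log-odds, and a change that is linear, b per quintile step.

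- Trend by period, 1 df, scores 1 to 5: non-centrality = w·b²·(4+1+0+1+4) = 10wb².
- Factor by period, 4 df: the same 10wb².
- Change in k versus 1, 1 df: [(k−1)b]² / (2/w) = w(k−1)²b²/2. For k = 5 this is 8wb², or 80% of the trend information.

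Set the trend test at 80% power: 10wb² = (1.960 + 0.842)² = 7.85.

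| Test of change | Non-centrality | Power |
|---|---|---|
| Trend, 1 df | 7.85 | 80% |
| Factor, 4 df | 7.85 | 59.5% |
| 5 vs 1 | 6.28 | 70.7% |
| 4 vs 1 | 3.53 | 46.8% |
| 3 vs 1 | 1.57 | 24.0% |
| 2 vs 1 | 0.39 | 9.6% |

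The last rows are low mainly because, under linearity, neighbouring quintiles truly differ less. The fair comparisons are the first three rows. At 90% trend power, the 4-df test has 74.0% and 5 vs 1 has 82.6%. At 99%, they have 94.8% and 97.0%.

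**Reading the two periods side by side.** The baseline is "Aggregate data for whole of 2019", 52 weeks. Lockdown runs from the week beginning 23 March to the week beginning 27 July: 126/7 + 1 = 19 weekly cohorts. Assume information is proportional to weeks. Then the variance of the lockdown log odds ratio is 52/19 = 2.737 times that of 2019, and its standard error is 1.654 times as large. Two 95% CIs fail to overlap only if

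|z| > 1.96 × (1 + 1.654) / √(1 + 2.737) = 2.69,

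which corresponds to alpha of about 0.007. For 5 vs 1 the expected z is √6.28 = 2.51, so power is Φ(2.51 − 2.69), about 43%, against 70.7% for a direct test of the same change.

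**When the change is not linear.** Scale the effect so that the 4-df test has 80% power.

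| Pattern of change | Trend | 5 vs 1 | 4 df |
|---|---|---|---|
| Only quintile 1, or only quintile 5 | 68.5% | 78.0% | 80% |
| Symmetric U | 5% | 5% | 80% |

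**Absolute scale.** The SAP gives no counts, so these are assumptions: N eligible a year, equal quintiles, 19/52 of N in lockdown, common uptake p, a linear change, and a true SIMD 5:1 ratio of odds ratios of 1.4. Then w = 1 / [1/(n₁p(1−p)) + 1/(n₂p(1−p))], with n₁ = N/5 and n₂ = n₁ × 19/52, and b = ln(1.4)/4 = 0.0841.

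| N | Uptake | Trend | 5 vs 1 | 4 df |
|---|---|---|---|---|
| 30,000 | 85% | 96.8% | 92.6% | 87.9% |
| 50,000 | 85% | 99.8% | 99.3% | 98.7% |
| 30,000 | 95% | 64.2% | 54.7% | 42.6% |
| 50,000 | 95% | 85.1% | 76.5% | 66.3% |
| 70,000 | 95% | 94.4% | 88.8% | 82.4% |

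**The case against.** The objective is exploratory and its outcome is defined by quintile. Coding SIMD as a factor assumes nothing about the shape of the change and is a sound choice. The non-linear patterns above show that a trend test is not uniformly better. The planned SIMD 5 versus 1 odds ratio already gives a gap between the extremes in each period. Because the quintiles are separate groups of children, a careful reader could also reconstruct each ratio of odds ratios and its CI from Table 7. All of this stands, and it limits the point to what is summarised, tested and reported.

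A reader might go further and infer that the plan throws the gradient away. The documents do not support that: all five quintiles are plotted and tabulated, and each is compared with the most deprived one in both periods.

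A reader might also infer that much of the power is lost. That is not supported either. Against the planned 5 versus 1 contrast the shortfall is about 9 points at 80% trend power, and only for a near-linear change. The 20-point gap is against a 4-df test that the SAP does not name. With a whole-population dataset the loss may be negligible, and the SAP has no counts or effect size from which to fix it.

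Nor does the SAP say that change will be judged by overlap of intervals. Its layout only leaves that reading open.

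What the objection does not answer is that the stated question, change in inequality, has no named estimate, interval or test.

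**Conclusion.** The point holds as a gap in estimation and reporting. It is not an error in the model. The plan asks whether inequality changed and reports nothing that measures the change, although its own interaction terms contain it. It also leaves the order of the quintiles unused in inference.

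For a near-linear change in log-odds with equal information per quintile, the cost relative to 80% trend power is about 9 points for 5 versus 1, about 20 points for a 4-df test, and about 37 points if the two periods' intervals are compared by eye (19/52 information assumed). These losses shrink where power is already high. They are most likely to matter for a vaccine with uptake near 95%. If only one end quintile changes, the ranking reverses. The improvement is worth making because it is cheap and lets the study answer its own question.

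**What to change.** 1. Keep the factor model, the bar plot and Table 7.
2. For each vaccine, report the period-by-SIMD interaction as four ratios of odds ratios (each quintile against SIMD 1, lockdown against 2019) with 95% CIs, and one joint 4-df test.
3. Pre-specify a gradient summary for each vaccine from a model with period, SIMD rank score and score-by-period. Report the 2019 slope, the lockdown slope and their difference with a 95% CI. Use one fixed set of scores in both periods, for example ridit scores from the 2019 eligible counts, so that a shift in quintile sizes does not pass for a change in inequality.
4. Give the slope on the odds-ratio scale. Also give it in percentage points, from a separate linear model or a derived calculation, because the objective's outcome is a difference in percentage uptake. Note that the null value is 0 on that scale, since the reporting rule mentions only 1.
5. Check departure from linearity against the quintile results, and say that the quintile results take precedence in interpretation if the pattern is not monotone.

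Cost: a few sentences in the SAP, one extra logistic model per vaccine, and the percentage-point calculation, all on counts already held. Downside: a linear score can miss a non-monotone change, which is why the quintile results and the linearity check stay.
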